### 2.11. Additional Assessment

Demographic profiles, special situations related to defecation during the study, including changes in dietary habits (e.g., eating spicy or oily foods or drinking), taking antibiotics, and any other reported situation will be recorded and assessed as needed.

### 2.12. Sample Size

This study is a clinical trial during which volunteers will consume a sample medication or placebo for 28 days and will be followed up for 42 days. The primary outcome measure is the weekly frequency of CSBMs. The expected weekly frequencies of CSBMs on day 28 are 1.1 in the control group and 4.1 in the probiotic group, with a between-group difference of 3. Given a standard deviation *S* = 6, *α* = 0.05, and *β* = 0.20, the sample size should be at least 63 volunteers per group, as calculated with the formula for statistically significant effectiveness. After considering the drop-out rate (20% or lower), the sample size should be 76 or more participants per group. The final sample size will be 100 participants per group for a total of 200 volunteers.

### 2.13. Compliance Monitoring and Withdrawal

The probiotics and placebo will be supplied as packages distributed in boxes. At the start of the administration period, the appropriate number of probiotic and placebo packages will be distributed to the participants. All used (empty) and unused packaging will be kept by volunteers. At the end of the administration period, these packages will be collected to verify the number of remaining packages and calculate the dosing rate. A dosing rate ≥80% indicates good compliance. A WeChat group will be established for the participants to improve compliance. The study personnel will post messages in the WeChat group to remind participants to take the samples as scheduled and complete the questionnaire. In addition, each participant will receive a reward of 300 RMB once they complete the follow-up.

Volunteers will be withdrawn from the trial for the following reasons: (1) continuous adverse reactions involving systemic infections that cannot be resolved after certain measures are taken, deleterious metabolic activities, excessive immune stimulation, gene transfer, and gastrointestinal side effects, which may be attributed to probiotics [60]; and (2) patients can actively withdraw from the trial at any time for any reason, and subsequent treatment will not be affected.

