**Method:**

A randomized, double-blind, placebo-controlled clinical trial is designed to study the efficiency and possible mechanism of action of probiotics for chronic constipation, in which 200 eligible volunteers with chronic constipation will be randomly assigned to a probiotic group (oral *Lactobacillus plantarum* P9 probiotic powder, 100 billion colony-forming units (CFUs)/day) or a placebo group. Volunteers, treatment distributors, data collectors, and data analysts will be blinded. The primary outcome is the weekly mean frequency of complete spontaneous bowel movements (CSBMs), and secondary outcomes include weekly mean frequency of CSBMs ≥3, weekly mean frequency of spontaneous bowel movements (SBMs), weekly mean stool appearance score, weekly mean difficulty of passing stool score, weekly percentage of volunteers who use auxiliary measures to assist with defecation (WPUAMA), quality-of-life (QOL) score, emotional status score, gut microbiome, and faecal metabolome. Each outcome measure will be assessed at the time points of preadministration (day 0), administration (day 14 and/or 28), and postadministration (day 42) to identify inter- and intragroup differences. Adverse events will be recorded to evaluate the safety of *L. plantarum* P9. *Discussion*. The protocol will provide methodological guidance for other similar studies, avoiding methodological bias and ultimately facilitating the formulation of consensus on the use of probiotics as a constipation-relieving agent. In addition, the results are more comprehensive than those of existing studies and may objectively and scientifically reflect the effectiveness of *L. plantarum* P9 on constipation. If the expected study findings are obtained, *L. plantarum* P9, taken as a probiotic, may become a complementary choice for chronically constipated patients. This trial is registered with Chinese Clinical Trial Registry (ChiCTR) (no. ChiCTR2000038396) registered on November 22, 2020, https://www.chictr.org.cn/showproj.aspx?proj=54024.

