### 2.5. Randomization and Blinding

Eligible volunteers will be assigned a unique serial number (e.g., 001, 002, 003, 004, 005……). The unique number will be used as the volunteers' ID throughout the study period to guarantee anonymity and confidentiality. For each of these unique numbers, a random sequence will be generated by the computer software *R* 4.1.0 and used to randomly assign the unique number (participant) to the probiotic group or the placebo group. During the study, the volunteer's treatment distributors, data collectors, and data analysts will be blinded to the randomization sequence. The randomization sequence will be maintained by an independent project administrator and will only be unblinded in the case of major safety issues or when performing the interim and final data analyses. Moreover, an independent project administrator will label the probiotics or placebo packages with unique numbers corresponding to random sequences in advance to achieve allocation concealment. During the period of administration, the distributor will distribute the treatment packages according to the unique number that corresponds to each participant.

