### 2.6. Study Interventions

The *L. plantarum* P9 and placebo powders will be manufactured in parallel and independently by Research and Development Department, Jiangzhong Pharmaceutical Company Limited (Nanchang, China). Briefly, the preparation procedure consists of three steps: weighing, mixing, and packaging. *L. plantarum* P9 powder is composed of 20% maltodextrin, 20% orange powder, 20% maltitol, and 40% *L. plantarum* P9, while placebo powder consists of 60% maltodextrin, 20% orange powder, and 20% maltitol. Raw materials for *L. plantarum* P9 and placebo powders are mixed using a Hopper mixer (hit-400) and sealed into 2 g packages. The temperature is controlled at 25 ± 2°C, and the relative humidity is less than 65% during the three steps. In the study, when the product of *L. plantarum* P9 powder is manufactured, a randomized sample is sent to Jinhua Yinhe Biotechnology Co., Ltd. (https://yinhewdy168.foodmate.net/) for quality inspection. The activity of probiotics is greater than 67 billion colony-forming units (CFUs)/g.

The study will include three phases (Table 1), including a screening period (an observation period prior to treatment administration), an observation period during administration, and an observation period after administration. The interventions in each phase will be administered as follows:Period of screening (preadministration observation period) (days 14 to 0): in this phase, volunteers will not receive the intended interventions, i.e., probiotics and placebo. Eligibility screening will be performed as described during volunteer recruitment (Table 1).Observation period during administration (days 0 to 28): (1) Probiotics group: volunteers will take 1 package of *L. plantarum* P9 powder directly or with warm water (below 40°C) on a full stomach at a dose of 100 billion CFUs per day; if antibiotics must be taken, probiotics should be taken 2 hours later. (2) Placebo group: volunteers will take the placebo in the same manner as the probiotics group. The placebo contains no probiotics but has the same appearance, packaging, and taste as the *L. plantarum* P9 powder.All remaining probiotics or placebo (unused) and empty (used) packages will be collected at the end of this period to monitor compliance. During the study, both probiotics and placebo will be stored in a cool, dry place away from direct sunlight.Postadministration observation period (days 29 to 42): no probiotics or placebo will be taken.

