### 2.8. Primary Outcome

A defecation diary developed with reference to the literature [32, 53–56] will be completed daily online by the participants (Figure 2). Based on the diary, the changes in primary and some of the secondary outcomes from day 0 (week 0) to day 42 (week 6) will be evaluated.The primary outcome measure is the weekly mean frequency of complete spontaneous bowel movements (CSBMs) [32, 54, 55].

A CSBM is defined as the ability to achieve a complete bowel movement without the use of any drugs or other auxiliary measures during the previous 24 hours. Based on the diary (Figure 2), the weekly mean frequency of CSBMs from day 0 (week 0) to day 14 (week 2), day 28 (week 4), and day 42 (week 6) will be evaluated [32, 54, 55] (Table 1).

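### One WeChat reminder group for the participants, naturally read as both arms together, gives volunteers a shared channel while they self-report the outcomes: a modest, cheaply avoided risk to blinding

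*Protocol article*

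**What the plan says.** Section 2.13 (Compliance Monitoring and Withdrawal) states: "A WeChat group will be established for the participants to improve compliance". It continues: "The study personnel will post messages in the WeChat group to remind participants to take the samples as scheduled and complete the questionnaire". This is the only use given for the group. The section does not say whether volunteers may post or contact each other, and it does not mention separate groups by arm.

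The Abstract sets out the blind: "Volunteers, treatment distributors, data collectors, and data analysts will be blinded". Under section 2.5 the packages carry unique participant numbers, and the randomization sequence stays with an independent project administrator. Section 2.6 says of the comparator: "The placebo contains no probiotics but has the same appearance, packaging, and taste as the *L. plantarum* P9 powder".

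On measurement, section 2.8 says that the defecation diary behind the primary outcome "will be completed daily online by the participants". A CSBM requires the movement to be complete, which only the volunteer can judge. Section 2.9 adds the PAC-QOL and the DASS-21, both questionnaires answered by the volunteer. Section 2.1 allows the product to be taken at home.

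**The concern.** When the outcome is the volunteer's own judgement, blinding matters most at the volunteer. Anything that helps volunteers work out their arm, or that sets common expectations about what the product does, can enter the data through the diary and questionnaires. A group holding both arms is such a channel, whatever it was set up for. Members could say whether they feel better, how often they go and what side effects they notice.

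Three things are at stake:

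- **The blind.** If the product has an effect, other volunteers' accounts give each member something to compare their own response with.
- **Expectation.** Talk of benefit or of disappointment can colour later entries in either arm.
- **Independence.** One volunteer's complaint can prompt another's. Section 2.10 grades the safety of the product from the adverse events observed, so prompted reports matter there as well as for efficacy.

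**Working it through.** The plan gives no figure on this point, so the check sets the relevant sections side by side.

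**1. Is it one group across arms?** Section 2.13 speaks of a group in the singular, for the participants, and then refers back to it as a single group. Arm-specific groups would need someone to sort volunteers by the randomization sequence, which section 2.5 keeps with the independent administrator. One group for both arms is therefore the natural reading. It is an inference, not the document's wording.

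**2. Does the document describe exchange between volunteers?** No. It describes reminders from staff. Exchange is neither described nor limited.

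**3. Which outcomes are exposed?** The primary outcome (2.8), the other diary outcomes, PAC-QOL and DASS-21 (2.9), and adverse-event reports (2.10). The microbiome and metabolome results come from laboratory analysis of stool samples and do not depend on what a volunteer reports.

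**4. Can the bias be signed or sized?** Let g1 and h1 be the shares of the probiotic arm who believe they take probiotic or placebo, and g0 and h0 the same shares in the placebo arm. Suppose a belief moves the reported weekly CSBM count by s, up for probiotic and down for placebo. The bias in the between-arm difference from guessing is

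B = s × [(g1 − h1) − (g0 − h0)].

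- *No true effect, matched products.* Both arms read the same messages and have the same experience, so g1 = g0 and h1 = h0. Then B = s × 0 = 0. Right and wrong guesses cancel between the arms.
- *A true effect.* The arms' experiences differ, and accounts from others help volunteers place their own. Then g1 − h1 can exceed g0 − h0, and B can differ from 0. Section 2.12 plans on 4.1 against 1.1 CSBMs per week, a difference of 4.1 − 1.1 = 3 with SD 6, or 3/6 = 0.5 SD. At that separation the arms overlap widely, so a volunteer's own response is a weak clue and a comparison with others could add to it.
- *Expectation without guessing.* If group talk shifts reports by e1 in the probiotic arm and e0 in the placebo arm, it adds e1 − e0. The sign is open: talk of benefit could lift placebo reports and shrink the difference.

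The documents give no value for s, g1, h1, g0, h0, e1 or e0, so neither direction nor size follows from them.

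**5. Is a change still useful?** Section 3.1 reports 130 enrolled, so 200 − 130 = 70 volunteers were still to come at that time, along with any enrolled volunteers who had not yet reached day 42.

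**The case against.** The strongest reply is that the point rests on what a condensed article does not say. Section 2.13 names one use, reminders from staff. Posting rules may stand in the full protocol, which is not shown. This stands in so far as no exchange between volunteers can be presumed. It does not remove the point, because the article itself chooses a group channel for a task that individual messages would also do.

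A second reply is that if the product works, volunteers may guess from their own response without any chat. This is partly true. The group adds a reference for comparison, and the effects on expectation and independence remain.

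A reader might also infer stronger things that the documents do not support:

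- *That volunteers could tell the products apart by comparing them.* Section 2.6 gives different compositions ("while placebo powder consists of 60% maltodextrin, 20% orange powder, and 20% maltitol", against 20% maltodextrin and 40% P9 in the active powder). But the same section states that appearance, packaging and taste match, and nothing says that the difference can be seen or tasted. If the match holds, comparing the product reveals nothing.
- *That the group breaks the promise of anonymity.* The words "to guarantee anonymity and confidentiality" in section 2.5 concern the unique number used as study ID. A chat group does not contradict them.
- *That the bias favours the product and raises the false-positive rate by a known amount.* Such a calculation assumes no true effect and yet counts more right guesses than wrong ones. With matched products and no effect, the two cancel.

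**Conclusion.** The point holds as a modest, avoidable risk to blinding and to independent self-reporting. It is not an error or a contradiction in the plan, and no break of the blind is shown. It rests on two inferences: that the one group holds both arms, and that members of a group channel can communicate unless this is restricted. No direction of bias, no shift in CSBMs per week and no change in error rate should be attached to it. The case for acting is that the outcomes are self-reported, the shared channel is not needed for its stated purpose, and the replacement costs little.

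**What to change.** Send the reminders as individual messages, or through a one-way channel in which only study staff can post. Apply this to volunteers now in the trial and to all who remain to be enrolled, in both arms alike. Tell volunteers to report perceived effects and adverse events in the diary or to staff only, and not to each other. One sentence in section 2.13 is enough to record this. Separate groups by arm would not be a good substitute, because setting them up would require use of the allocation list.

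Optionally, add one item on day 28, alongside the online DASS-21, asking which product the volunteer believes was taken. This would give some evidence on how well the blind held. It should be read with care, since a true effect can itself produce correct guesses.

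The cost is a messaging setting, one sentence and, if wanted, one question. The downsides are small: some peer encouragement is lost, and the reminder channel changes partway through enrolment. That change falls equally on both arms, and the stated reminder function is kept.

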
### 2.10. Safety Evaluation

All related clinical trials have reported that probiotics are safe and do not induce significant adverse events compared with the placebo group. However, four types of adverse reactions related to probiotics should be considered, including symptoms that may be attributed to systemic infections, deleterious metabolic activities, excessive immune stimulation, and gastrointestinal side effects [60], which will be collected as possible adverse events during the study. Severe adverse events are those adverse events leading to study withdrawal, e.g., hospitalization, disability, mortal danger, or death. All adverse events, including symptoms, time of onset, duration, causal relationship to interventions, and measures taken, will be accurately recorded during the study. Any serious adverse events will be recorded along with the corresponding criteria and emergency measures and will be promptly reported to the Medical Ethics Committee of the First Affiliated Hospital of Nanchang University within 24 hours; a separate study report will be prepared. Based on the adverse events observed during the study, the safety of the probiotics will be evaluated as excellent (safe, without any adverse events), good (relatively safe with moderate adverse events that resolve on their own without any specific treatment and do not result in study withdrawal), conditional (adverse events that resolve after certain measures are taken and allow continued participation in the study), or unsafe (adverse events that result in study withdrawal) [61].

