### 2.15. Statistical Analysis

The intention-to-treat (ITT) analysis will be conducted between the two groups. Then, the following four data sets will be used for the per-protocol (PP) analysis: (1) the data from all participants who completed the follow-up and (2) a subgroup analysis regarding levels of compliance (≥80%, 60–80%, and <60%) to validate the robustness of the results. The hypothesis will be tested using the methods described below during the ITT and PP analyses.

First, the Wilcoxon signed-rank sum test will be used for the outcome measures, including the weekly mean frequency of CSBMs, weekly mean stool appearance score, weekly mean difficulty of passing stool score, weekly mean frequency of SBMs, QOL score, and emotional status score, at each observation point to analyse the intergroup differences in each outcome measure. The chi-square (*χ*^2^) test will be used for the outcome measures, namely, the percentage of volunteers with a weekly mean frequency of CSBMs ≥3 and WPUAMA, at each observation point. In the analyses, the *P* value indicating statistical significance will be set to 0.05.

Then, the Kruskal–Wallis rank sum test will be used for multiple comparisons of outcome measures, including the weekly mean frequency of CSBMs, weekly mean stool appearance score, weekly mean difficulty of passing stool score, weekly mean frequency of SBMs, QOL score, and emotional status score, and the *χ*^2^ test will be used for multiple comparisons of outcome measures, including percentage of volunteers with a weekly mean frequency of CSBMs ≥3 and WPUAMA, at each observation point to identify the intragroup changing trends in consecutive phases, namely, pre-, during, and postprobiotic administration. In the analyses, the *P* value indicating statistical significance will be adjusted to 0.05/[*k* (*k* −1)/2], where *k* is the number of sample groups included in the comparison.

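### Section 2.13 withdraws volunteers with continuous adverse reactions from the trial rather than from product alone, which puts their later outcome and safety data at risk

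*Protocol article*

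**What the plan says.** Section 2.13 (Compliance Monitoring and Withdrawal) states: "Volunteers will be withdrawn from the trial for the following reasons". Two reasons follow.

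- The first covers "continuous adverse reactions involving systemic infections that cannot be resolved after certain measures are taken", together with metabolic, immune, gene-transfer and gastrointestinal effects that may be attributed to probiotics.
- The second is the volunteer's own choice: "patients can actively withdraw from the trial at any time for any reason, and subsequent treatment will not be affected".

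Section 2.10 (Safety Evaluation) uses the same idea twice. It says "Severe adverse events are those adverse events leading to study withdrawal", and its worst safety grade is "unsafe (adverse events that result in study withdrawal"). The grade just above, conditional, is for events that settle after measures are taken and let the volunteer stay in the study. The same section requires the duration of every adverse event to be recorded.

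Section 2.15 (Statistical Analysis) states: "The intention-to-treat (ITT) analysis will be conducted between the two groups". It applies rank and chi-square tests at each observation point. Among its per-protocol sets it lists "the data from all participants who completed the follow-up".

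Section 2.12 gives the time frame: "volunteers will consume a sample medication or placebo for 28 days and will be followed up for 42 days". Table 1 schedules adverse events on days 14, 28 and 42.

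**The concern.** The first reason in 2.13 is a removal by rule, listed apart from the volunteer's own decision to leave. It acts on events that may be caused by the product, so it may act more often in one arm than in the other. The article does not separate stopping the product from ending observation, and 2.10 points to the two being the same thing.

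Two things are at stake. The first is efficacy: a test run at day 28 or day 42 needs a value at that day, and a volunteer removed earlier has none unless one is imputed. If those removed differ from those who stay, and the arms lose different numbers or kinds of volunteers, the comparison at later time points is no longer the randomised one. The second is safety: reactions that are continuous by definition are those whose duration most needs following, and the rule leaves no stated route for collecting it after withdrawal.

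**Working it through.** **Reading the sections together.**

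1. In 2.13 the object of withdrawal is the trial. Product alone is not mentioned.
2. In 2.10 the conditional grade keeps the volunteer in the study and the unsafe grade does not. Withdrawal therefore means, on its ordinary reading, that participation ends.
3. Observation off product is already part of the design: section 2.6 takes everyone off product on days 29 to 42, and 2.15 plans an analysis of volunteers with a dosing rate below 60%. Having stopped product is thus no reason in itself to stop observing.

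**The plan's own figure.** Inputs from 2.12: expected day-28 CSBMs 4.1 (probiotic) and 1.1 (control), difference d = 3, S = 6, α = 0.05 (two-sided reproduces the figure), power 80%.

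n = 2 × (1.960 + 0.842)² × 6² / 3² = 62.8, so 63 per group. This matches. At 100 per group the power is 94.2%, and at 80 per group (20% lost) it is 88.5%. Power is not the problem; possible bias is.

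**Illustration of the bias.** The following are assumptions, not figures in the article: a share w of the probiotic arm is withdrawn for reactions before day 28, nobody on placebo is, those withdrawn would have had the control value of 1.1, and their missing values are simply dropped.

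*If 4.1 is the mean of those who remain*, the all-randomised difference is (1 − w) × 4.1 + w × 1.1 − 1.1:

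- w = 5%: 0.95 × 4.1 + 0.05 × 1.1 − 1.1 = 2.85; overstatement 3.0 / 2.85 = 1.05.
- w = 10%: 0.90 × 4.1 + 0.10 × 1.1 − 1.1 = 2.70; overstatement 3.0 / 2.70 = 1.11.

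*If 4.1 is the mean of all randomised*, the difference among those who remain is (4.1 − w × 1.1) / (1 − w) − 1.1:

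- w = 2%: 3.06
- w = 5%: 3.16
- w = 10%: 3.33
- w = 20%: 3.75

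These compare with a true 3.0. Both anchors give an overstatement of about 5% to 11% for w between 5% and 10%.

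**Withdrawals in both arms.** Placebo withdrawals offset the bias only so far as those volunteers would have done worse than the rest of their arm. If they would have had 1.1, the placebo mean does not move and there is no offset. Under the first anchor, take 10% withdrawn in each arm and the placebo ones at the lowest possible value, 0. The placebo mean is 0.90 × 1.1 = 0.99, the all-randomised difference is 3.80 − 0.99 = 2.81, and the overstatement falls to 3.0 / 2.81 = 1.07.

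**Scale.** With 100 per group the standard error of the difference is 6 × √(2/100) = 0.85. Under the first anchor the bias is 0.15 to 0.30 CSBMs a week, or 0.15 / 0.85 = 0.18 to 0.30 / 0.85 = 0.35 of a standard error.

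**The case against.** The strongest reply is that data loss is inferred. Section 2.13 neither says that collection stops nor discards what was already collected, and a journal article may leave follow-up after withdrawal to the full protocol or the consent form. In part this stands: diary entries and adverse-event records up to withdrawal are kept, so only later data are at risk. It does not remove the point, because 2.13 states a rule rather than being silent, and followed as written with 2.10 it ends observation. An analysis plan could say how to impute, but it could not recover diaries or reports that were never collected.

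A reader might infer that the ITT comparison is confined to volunteers who tolerated treatment. The article does not support that. Section 2.15 places completers among the per-protocol sets, distinct from ITT, and keeps poor compliers in view. ITT would shrink in that way only at time points after withdrawal and only if missing values were dropped, which the article does not say.

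A reader might also infer that the most important adverse events go unrecorded. That too goes too far. Section 2.10 requires onset, causal relationship and measures taken for all events, with prompt reporting of serious ones, so the event that triggers withdrawal is captured. What is exposed is its later course.

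On size, several objections hold. The 5% to 10% rate has no source in the article, and 2.10 reports that related trials found no significant excess of adverse events over placebo. The rule is narrow. Under 2.14, a severe event related to the probiotic would lead the data management team to suggest terminating the study, so several such withdrawals might raise that question before the final analysis. The direction is not assured either: if some gastrointestinal reactions meant more frequent stools, dropping those volunteers could lower the probiotic mean.

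**Conclusion.** The point holds as a flaw in a data-collection rule, not as proof of a biased result. Sections 2.13 and 2.10 merge stopping product with leaving follow-up, for a reason that may be related to arm. That puts data after withdrawal at risk and sits badly with the planned ITT comparison at later observation points and with recording adverse-event duration to day 42.

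The overstatement of about 5% to 11% rests wholly on assumptions: withdrawals of 5% to 10%, confined to the probiotic arm, with control-level outcomes and no imputation. It shrinks with fewer withdrawals, and with balanced ones where the placebo volunteers withdrawn would also have done worse than their arm. Even at its largest in this range it is well inside one standard error. The case for change is that prevention is cheap, while data not collected cannot be recovered.

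**What to change.** Leave the reasons for stopping product exactly as they are; when product should stop is a clinical matter and is not judged here. Reword 2.13 so that a volunteer who meets the first reason stops product only, and continues the diary, PAC-QOL, DASS-21 and adverse-event reporting to day 42 unless he or she withdraws consent for data collection. Align the references to study withdrawal in 2.10 with that distinction, and state in 2.15 that these data are included in the ITT analysis.

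The cost is a protocol and consent amendment and a small added burden on the volunteers concerned. The diary and DASS-21 are already collected online (section 2.14). Some volunteers will decline. The change helps only those still in the trial or yet to enrol: section 3.1 reports 130 enrolled of the 200 planned.
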